# Cognitive training and promoting a healthy lifestyle for individuals with isolated REM sleep behavior disorder: study protocol of the delayed-start randomized controlled trial CogTrAiL-RBD

**DOI:** 10.1186/s13063-024-08265-9

**Published:** 2024-06-28

**Keywords:** Isolated REM sleep behavior disorder, Cognitive training, Randomized controlled trial

## Abstract

**Background:**

Isolated REM sleep behavior disorder (iRBD) is an early α-synucleinopathy often accompanied by incipient cognitive impairment. As executive dysfunctions predict earlier phenotypic conversion from iRBD to Parkinson’s disease and Lewy body dementia, cognitive training focusing on executive functions could have disease-modifying effects for individuals with iRBD.

**Methods:**

The study CogTrAiL-RBD investigates the short- and long-term effectiveness and the feasibility and underlying neural mechanisms of a cognitive training intervention for individuals with iRBD. The intervention consists of a 5-week digital cognitive training accompanied by a module promoting a healthy, active lifestyle. In this monocentric, single-blinded, delayed-start randomized controlled trial, the intervention’s effectiveness will be evaluated compared to an initially passive control group that receives the intervention in the second, open-label phase of the study. Eighty individuals with iRBD confirmed by polysomnography will be consecutively recruited from the continuously expanding iRBD cohort at the University Hospital Cologne. The evaluation will focus on cognition and additional neuropsychological and motor variables. Furthermore, the study will examine the feasibility of the intervention, effects on physical activity assessed by accelerometry, and interrogate the intervention’s neural effects using magnetic resonance imaging and polysomnography. Besides, a healthy, age-matched control group (HC) will be examined at the first assessment time point, enabling a cross-sectional comparison between individuals with iRBD and HC.

**Discussion:**

This study will provide insights into whether cognitive training and psychoeducation on a healthy, active lifestyle have short- and long-term (neuro-)protective effects for individuals with iRBD.

**Trial registration:**

The study was prospectively registered in the German Clinical Trial Register (DRKS00024898) on 2022–03-11, https://drks.de/search/de/trial/DRKS00024898. Protocol version: V5 2023–04-24.

**Supplementary Information:**

The online version contains supplementary material available at 10.1186/s13063-024-08265-9.

## Background

REM (rapid eye movement) sleep behavior disorder (RBD) is a parasomnia characterized by loss of muscle atonia and dream enactment during REM sleep [1, 2]. Isolated RBD (iRBD) is an early α-synucleinopathy [3–5] and may constitute a prodromal stage of Parkinson’s disease (PD), dementia with Lewy bodies (DLB), or multiple system atrophy (MSA) [6–10]. To date, iRBD is the most specific marker to indicate the prodromal stage of PD and a well-recognized feature in prodromal DLB and MSA [6–10]. Within 15 years after diagnosis, up to 80% of individuals with iRBD exhibit phenotypic conversion to PD, DLB, or MSA, with approximately 95% of the converters eventually developing PD or DLB [10, 11].

In the prodromal PD stage [12, 13], and particularly in individuals with iRBD [14, 15], cognitive alterations have been reported. As expected by definition, a recent multicenter data analysis by the International REM Sleep Behavior Disorder Study Group suggests that the only reliable clinical marker differentiating between individuals with iRBD who develop PD or DLB first is the higher prevalence and rate of cognitive decline in DLB-converters [11]. Furthermore, individuals with iRBD converting to PD are more likely to develop a more aggressive “diffuse malignant” PD subtype, characterized by a higher burden of non-motor symptoms, particularly cognitive dysfunction and eventually PD dementia (PDD) [11, 16–18]. Cognitive decline is one of the most debilitating non-motor symptoms in PD [19], as it greatly impacts the patients’ quality of life and independence in activities of daily living and increases the burden on caregivers, care providers, and the public healthcare system [20, 21].

Compared to healthy control individuals (HC), meta-analytical evidence suggests that individuals with iRBD show alterations of medium effect sizes in global cognition, executive functions, and memory [15]. Furthermore, impairments in global cognition and executive functions in individuals with iRBD have been identified as risk factors for conversion within the α-synucleinopathies [7, 14, 15]. Cognitive alterations in individuals with iRBD are accompanied by functional and structural alterations in the brain, pointing to early neurodegeneration at this stage [22–25]. Therefore, iRBD not only represents a clinical syndrome but may offer a window of opportunity for disease-modifying, potentially neuroprotective pharmacological and non-pharmacological interventions [10, 26, 27]. The development of neuroprotective interventions and their evaluation in clinical trials is of outstanding clinical interest. It could alleviate ethical concerns associated with an early iRBD diagnosis, as the latter informs individuals about their increased risk of developing PD, DLB, or MSA without available targeted interventions [27–29]. For Alzheimer’s disease, large (secondary) prevention trials already exist that focus on non-pharmacological multi-domain interventions in at-risk cohorts [30–32]. These interventions aim to promote a healthy, active lifestyle in the domains of cognition (e.g., through cognitive training), exercise (e.g., through physical exercise interventions), and nutrition (e.g., through information, consulting, and monitoring). These interventions have demonstrated long-lasting effects, particularly concerning cognitive functions [30, 32, 33].

Non-pharmacological interventions, especially cognitive interventions, have the potential to preserve cognitive functions in both healthy and pathological aging, thereby enhancing the quality of life and independence of older individuals. In a systematic review summarizing 46 meta-analyses on the effectiveness of cognitive interventions, Gavelin et al. [34] demonstrated that the existing evidence suggests reliable positive effects of cognitive training on global cognition of older adults. Meta-analyses have also shown positive training effects induced by cognitive training specifically for individuals with PD [35–37]. These effects were particularly evident in vulnerable cognitive domains in PD, such as executive functions [35–37]. This is particularly important as executive dysfunctions predict earlier conversion within α-synucleinopathies [7, 14, 15]. Therefore, cognitive training focusing on executive functions could have disease-modifying effects for individuals with iRBD. This hypothesis is supported by studies showing that cognitive training interventions cannot only improve cognitive functions at the behavioral level, but may also lead to network optimizations: Meta-analytically, reduced task-related activation in cortical areas along with increased task-related activation in subcortical areas was observed after cognitive training, which is interpreted as an increase in neural efficiency [38, 39]. Aside from the growing evidence for overall beneficial behavioral and neural effects of cognitive training, the individual responsiveness to cognitive interventions may be heterogeneous. Thus, only an in-depth characterization of the participants’ baseline prerequisites, e.g., in terms of demographic, clinical, (neuro-)psychological, or structural and functional brain parameters, may foster the understanding of who benefits most from cognitive interventions and help to tailor interventions individually [40–43].

Individuals with iRBD and individuals with PD plus RBD often exhibit severe degeneration of the noradrenergic locus coeruleus, which is an established predictor of cognitive decline in PD [44, 45]; however, the relevance of the noradrenergic system in the context of cognitive training is unknown. Given that behavioral effects of cognitive training can endure up to 10 years in healthy older individuals [33], it is unsurprising that this kind of intervention might trigger not only functional but also structural brain changes (e.g., gray matter and cortical volume increases) [46]. However, no data on the plasticity of white and gray matter microstructure upon a cognitive intervention in iRBD is available, and data in PD remains scarce and inconclusive [47, 48]. More studies elucidating the mechanisms of neural plasticity induced by cognitive interventions via longitudinal imaging before and after cognitive training are warranted, particularly for individuals with iRBD.

A plethora of data suggests a mutual relationship between sleep and cognition in health and disease [49], and the deterioration of sleep macro- and microparameters in individuals with PD has been demonstrated repeatedly [1, 50, 51]. Furthermore, individuals with PD with a lower amount of slow-wave sleep are prone to a faster motor progression as well as poorer cognitive performance [52]. Hence, sleep macro- and microparameters may constitute a relevant driver of the responsiveness to cognitive interventions in iRBD, and data on sleep plasticity are warranted to guide future interventional trials.

The study CogTrAiL-RBD (Cognitive Training and a Healthy, Active Lifestyle Program for Patients with isolated REM Sleep Behavior Disorder) aims to investigate the short- and long-term effectiveness and the feasibility of a cognitive training intervention for individuals with iRBD. The intervention consists of (i) a 5-week digital cognitive training and (ii) a module promoting a healthy, active lifestyle, which includes psychoeducational information on cognitive, physical, and social lifestyle activities, as well as nutrition, along with concurrent monitoring of these domains using a digital activity diary over a period of 15 months.

Within the framework of a monocentric, single-blinded, delayed-start randomized controlled trial, the intervention’s effectiveness will be evaluated compared to an initially passive control group that receives the intervention in the second, open-label phase of the study. The evaluation will focus on cognition and additional neuropsychological and motor variables. Furthermore, the general feasibility of the intervention for individuals with iRBD will be investigated. Additionally, the study will examine the neural effects of the intervention by magnetic resonance imaging (MRI) and overnight polysomnography. A healthy, age-matched control group will be examined at the first assessment time point, enabling a cross-sectional comparison between the individuals with iRBD and HC. Reporting of this study protocol follows the “Standard Protocol Items: Recommendations for Interventional Trials” (SPIRIT) checklist [53]. A schematic figure of the study design can be found in Appendix Figure A-1.

## Methods/design

### Study design and setting

The study CogTrAiL-RBD is designed as a monocentric, single-blinded, delayed-start randomized controlled trial with two study arms aiming to consecutively recruit 80 individuals with iRBD confirmed by polysomnography from the continuously expanding local iRBD cohort at the University Hospital Cologne in Germany [54]. Participants will be randomly assigned to either the early intervention group or a delayed-start control group. Forty participants will be randomly assigned to each group (parallel group phase, superiority). The delayed-start control group will receive the same intervention after a 6-month waiting period, with the early intervention group undergoing the intervention for a second time to separate symptomatic from potentially disease-modifying effects (open-label phase, exploratory) [55].

Figure A-1 presents the schematic trial design and Appendix Figure A-1 further illustrates the timeline for participants. At baseline assessment (t0, week 0), the study will be explained to the participants. Subsequently, the participants will provide written informed consent and answer to a demographic interview. All participants with iRBD will undergo comprehensive clinical and neuropsychological assessments at the t0 visit and 6 weeks post allocation (posttest I, t1, week 6). A follow-up assessment (follow-up I, t2, week 33) will be conducted after 6 months. Subsequently, the second intervention phase for both the early intervention group and the delayed-start control group begins, followed by another clinical and neuropsychological assessment (posttest II, t3, week 39). Finally, a follow-up assessment (follow-up II, t4, week 66) will take place after an additional 6 months.

There are three optional study modules for individuals with iRBD that accompany the mandatory clinical and neuropsychological assessments: (i) the MRI module consisting of structural and functional MRI at each assessment time point; (ii) the accelerometry module consisting of physical activity tracking with accelerometers at each assessment time point; and (iii) the polysomnography module including two polysomnographies, one before the start of the intervention and one within the last 2 weeks of the intervention. Additionally, an age- and sex-matched HC group will be examined at the first assessment time point, participating in the comprehensive clinical and neuropsychological assessments, the MRI module and the accelerometry module.

### Recruitment

Individuals with iRBD are recruited from the local iRBD cohort at the University Hospital Cologne, Germany, which is continuously expanding through active recruitment efforts. The recruitment strategy for the local iRBD cohort has been described in Seger et al. [54]. Those who consented to be contacted for study participation during the annual iRBD consultation hours are directly approached by the CogTrAiL-RBD study personnel via telephone. The subjects are provided with a comprehensive information sheet outlining the details of CogTrAiL-RBD, and, if interested in study participation, a structured telephone interview is conducted. The HC group will be recruited via email newsletters, flyers, and newspaper advertisements.

### Inclusion and exclusion criteria

The following inclusion criteria are applied for individuals with iRBD: (i) polysomnography-proven diagnosis of iRBD, (ii) age between 40 and 80 years, (iii) normal or corrected-to-normal vision and hearing, (iv) German as native tongue or sufficient proficiency in German, and (v) access to a local computer with access to the internet. Exclusion criteria for individuals with iRBD are (i) severe cognitive dysfunctions (Montréal Cognitive Assessment, MoCA, ≤ 22) [56] interfering with the ability to give informed consent, (ii) significant neurological and psychiatric concomitant diseases, and for those willing to participate in the optional MRI module (iii) contraindications for MRI. Except for the polysomnography-proven diagnosis of iRBD, the same in- and exclusion criteria are applied for HC plus the absence of a diagnosis of a movement disorder or signs of iRBD or any other psychiatric and neurological condition as assessed by medical history.

### Sample size and power calculation

To determine an adequate sample size, an a priori power analysis was conducted with G*Power [57] (http://www.gpower.hhu.de). The study will be powered to reliably detect behavioral effects in the domain of executive functions (the primary outcome) in the first parallel-group phase of the randomized controlled trial in individuals with iRBD. According to two meta-analyses on cognitive training in healthy older adults [58] and individuals with PD [36], we expect a medium effect size (Cohen’s *d* = 0.5) in the domain of executive functions. With a two-sided *α*-level of 0.05 and 80% power, the minimum sample size comparing the difference between two independent groups (allocation ratio 1:1) with a *t*-test is *N* = 128 (i.e., *n* = 64 per group).

We applied the correction formula of Borm et al. [59], acknowledging the increase of precision in estimating a treatment effect when the correlation between the outcome measure at baseline and retest ($$\rho$$) by ANCOVA is considered: *n*_cor_ = *n**$$\sqrt{1-{\rho }^{2}}$$. A meta-analysis [60] on the reliability of neuropsychological measures identified particularly high correlations between baseline and retest measures of executive functions (Pearson’s *r* ≥ 0.80). Following, the G*Power estimate of *n* = 64 per group was corrected by the factor $$\sqrt{1-{0.8}^{2}}=0.6$$, resulting in a minimum sample size of *n*_cor_ = 38 per group, i.e., a total sample of *N*_cor_ = 76. The estimated dropout rate for the first parallel-group phase of the randomized controlled trial of the present trial is 5%, based on previous experiences with a similar intervention in individuals with PD [61]. Following, we aim to recruit *N* = 80 (= 76/0.95) individuals with iRBD for the present trial.

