For the analysis of training effects in the primary and secondary outcomes, linear mixed effects (LME) models will be used. Dependent variables are the respective primary or secondary outcome measures. All dependent variables are assessed at three points of time. The LME models include time (t0, t1, t2), group (early intervention group and delayed-start control group), and the interaction between time and group (time*group) as fixed factors. Furthermore, participants and time are included as random factors. Models will be estimated using the *lmer()* function of the *lme4*-package employing restricted maximum likelihood estimation [119]. Model fit will be evaluated using marginal *R*^2^, which considers the variance of the fixed effects only, and conditional *R*^2^, which accounts for both fixed and random effects. *t*-Tests will be conducted to assess the significance of single coefficients. For the interaction effects, relative effect sizes with 95% confidence intervals will be reported and defined as the difference of the mean change over time in the early intervention group minus mean change over time in the delayed-start control group divided by the pooled baseline standard deviation of the cohort. Within the analysis of training effects, we will pursue an intention-to-treat approach. No imputation methods will be used, as one strength of LME models is their ability to deal with unbalanced designs, for example, due to missing values in longitudinal data.

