## Discussion

CogTrAiL-RBD is to the best of our knowledge the first cognitive intervention study, additionally promoting a healthy, active lifestyle, for individuals with iRBD. With the longitudinal, multi-modal data collection, it will not only be possible to gain insights on the effectiveness of such an intervention at this at-risk group for the development of PD, DLB, and MSA and corresponding cognitive impairment, but we will also develop a better understanding on the underlying mechanisms of behavioral training effects. The trial is powered to detect behavioral differences in the first parallel-group phase of the randomized controlled trial. Following, any analyses focusing on the second open-label phase are fully exploratory, constituting a limitation to the trial. From a clinicians’ and patients’ perspective, this trial is pioneering, as it could alleviate ethical concerns associated with an early iRBD diagnosis [27–29]. Cognitive training combined with psychoeducation on a healthy, active lifestyle would be a low-threshold and safe intervention approach for this at-risk group to counteract cognitive decline.

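### The baseline-adjustment step multiplies n by √(1−ρ²) instead of 1−ρ², so 38 per group is not the minimum for 80% power; the trial is oversized under its own inputs, not underpowered

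*Protocol article*

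**What the plan says.** The section Sample size and power calculation starts from a two-group t-test. On effect size it says "we expect a medium effect size (Cohen’s *d* = 0.5) in the domain of executive functions". The error rates are set by "With a two-sided *α*-level of 0.05 and 80% power". The unadjusted requirement for "comparing the difference between two independent groups (allocation ratio 1:1") "is *N* = 128 (i.e., *n* = 64 per group").

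The plan then applies a correction, "acknowledging the increase of precision in estimating a treatment effect when the correlation between the outcome measure at baseline and retest" is taken into account by ANCOVA. The general formula is printed as n_cor = n·√(1−ρ²). A meta-analysis is cited for r ≥ 0.80, and 0.8 is used. The figure of "64 per group was corrected by the factor" 0.6, which gives 38 per group, 76 in total, described as the minimum. Allowing for 5% dropout, 76/0.95 = 80.

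The section Statistical analyses plans a linear mixed model with time (t0, t1, t2), group and their interaction. The effect size is the difference in mean change "divided by the pooled baseline standard deviation of the cohort".

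**The concern.** Adjusting for a baseline that correlates ρ with the outcome leaves a residual variance of σ²(1−ρ²) and a residual SD of σ√(1−ρ²). For a fixed difference, n is proportional to the variance. The plan multiplies n by the SD factor, so it credits baseline adjustment with less than it earns.

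The stated link between N = 76, d = 0.5, ρ = 0.8 and 80% power is therefore wrong, and it is the justification given for the enrolment target. Two readings suffer:

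- **A null result.** It would exclude smaller effects than the power statement suggests.
- **The margin on ρ.** As written, 80% power seems to be lost as soon as ρ falls below 0.8. In fact there is slack, and its amount depends on the analysis used. This matters because 0.8 comes from a meta-analysis of neuropsychological measures, not from this executive composite in iRBD.

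**Working it through.** **Inputs**, all from Sample size and power calculation: d = 0.5 (unadjusted SD set to 1), two-sided α = 0.05, power 80%, 1:1 allocation, ρ = 0.8, dropout 5%. Power is computed from the noncentral t distribution.

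**1. The plan's own figures.**
- Unadjusted t-test: 64 per group gives 80.1% power. The starting figure reproduces.
- 64 × √(1−0.64) = 64 × 0.6 = 38.4, printed as 38; 2 × 38 = 76; 76/0.95 = 80. The printed numbers follow, but only with the square root. Since it stands in both the general formula and the worked number, it is not a fault of text extraction.

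**2. ANCOVA on baseline.**
- Variance factor: 1−ρ² = 1−0.64 = 0.36.
- 64 × 0.36 = 23.04, so 24 per group.
- Direct check with standardised difference 0.5/0.6 = 0.833 and 2n−3 degrees of freedom: 23 per group gives 78.9%, 24 gives 80.6%. The minimum is 24 (N = 48; 48/0.95 = 50.5, so 51 with dropout).
- At 38 per group: 94.8%.

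**3. Change score**, as an approximation to the planned time-by-group contrast (complete data, equal variances at the two visits, ρ = 0.8 between them).
- Variance factor: 2(1−ρ) = 0.4; standardised difference 0.5/√0.4 = 0.791.
- 26 per group gives 79.8%, 27 gives 81.3%. The minimum is 27.
- At 38 per group: 92.5%.

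**4. What 38 evaluable per group delivers.**

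| | Change score | ANCOVA |
|---|---|---|
| Power at d = 0.5, ρ = 0.8 | 92.5% | 94.8% |
| Lowest ρ for 80% power at d = 0.5 | 0.71 | 0.64 |
| d detectable with 80% power at ρ = 0.8 | 0.41 | 0.39 |
| Power at d = 0.5, ρ = 0.64 | 72% | 80% |
| Power at d = 0.5, ρ = 0.6 | 67% | 77% |

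**5. Variants.** By the normal approximation with the 0.36 factor, a one-sided test needs 18 per group, 90% power needs 31 and 95% power needs 38. None of the variants tried gives 38 at 80% power.

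**The case against.** The strongest reply is that the error is harmless. It enlarges the trial, and the cited correlations are 0.80 or higher, so 0.8 is the low end of the cited range. The article describes the risks as minimal, and 68 of the 80 participants had been recruited at the time of revision. No analysis, error rate or procedure depends on the formula. All of this stands. It limits the consequence to a misdescribed power statement, but does not make that statement right.

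A reader who sees that the stated 80% does not match might infer that the trial is underpowered. The documents do not support that: under the plan's inputs both readings of the analysis exceed 90%. Power would fall below 80% only if ρ were under about 0.71 (change score) or 0.64 (ANCOVA), and nothing in the article says that it is.

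A reader might also infer that the Discussion is wrong where it says: "The trial is powered to detect behavioral differences in the first parallel-group phase of the randomized controlled trial". That sentence remains true after the correction.

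A third tempting step is to replace 80% by the ANCOVA figure of about 95%. The planned model carries t0 as an outcome level and tests a time-by-group interaction, so that figure does not describe it. To say that 80% power holds down to ρ = 0.64 would be wrong for a change-score type of analysis, where power at that correlation is about 72%. The change-score figures are themselves approximate, because the article does not spell out the random-effects structure or say which visit carries the primary contrast.

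The rounding of 38.4 down to 38 is immaterial once the requirement is 24 to 27 per group.

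**Conclusion.** The printed correction is wrong as a sample-size formula, and 38 per group is not the minimum for 80% power at the stated inputs. The minimum is 24 per group for ANCOVA and about 27 for a change-score comparison. The direction is conservative, so N = 80 is adequate if ρ = 0.8 holds.

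The ANCOVA result rests only on the plan's d, ρ, α and power and on the residual variance σ²(1−ρ²). It does not depend on what the cited source for the correction says. The change-score result also assumes complete data, equal variances, and ρ = 0.8 for the contrast tested.

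**What to change.** - Replace the formula by n_cor = n(1−ρ²), and stop calling 38 per group the minimum for 80% power.
- Keep N = 80 and restate what 38 evaluable per group provides under the planned analysis. If the time-by-group mixed model is kept: approximately 92.5% power at d = 0.5 and ρ = 0.8, 80% power down to ρ of about 0.71, and d of about 0.41 detectable with 80% power at ρ = 0.8. State the change-score approximation behind these figures.
- Quote about 95%, ρ about 0.64 and d about 0.39 only if the primary analysis is changed to adjust for baseline.

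The cost is one corrected formula and one restated power sentence. Enrolment and trial conduct do not change.
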